## Methods

### Ethics Approval

Ethical approval for this study has been granted by the Edith Cowan University Human Research Ethics Committee (reference STREAM 22000). All participants will provide written informed consent.

### Recruitment

Older adults with and those without self-reported poor sleep will be recruited from the community in Western Australia, with advertisements being displayed on the Sleep Health Foundation website and social media sites such as Facebook, as well as in community centers and senior citizen organizations. Participants are eligible to take part if they are aged 60-80 years and ordinarily reside in Western Australia, if they have not been diagnosed with an existing sleep disorder other than insomnia, if they have not been diagnosed with a severe psychiatric or cognitive disorder, if they have not engaged in regular shift work in the past year, and if they have not been diagnosed with epilepsy or are at high risk of falling.

Screening for the presence of obstructive sleep apnea, which is common among older adults, will be conducted using the STOP-Bang (snoring, tiredness, observed apnea, high BP, BMI, age, neck circumference, and male gender) questionnaire, a brief self-report instrument [41]. The STOP-Bang questionnaire has demonstrated a high sensitivity of 84% in detecting obstructive sleep apnea [41]. Participants that score 0 to 2 on the instrument are considered unlikely to present with moderate to severe sleep apnea. Participants who took sleep medication were not excluded, as CBT-I has shown to be effective in those who take sleep medication [12]. However, the type, dosage, and frequency of any medication taken by participants were recorded as part of the demographic assessment.

### Design

Study participants will be required to complete a web-based questionnaire battery at baseline and following the intervention. It is estimated that it will take approximately 20-25 minutes to complete the questionnaire battery. Sleep-related dysfunctional beliefs will be assessed using the Dysfunctional Beliefs and Attitudes about Sleep (DBAS-16) scale [42]. The DBAS-16 was developed to examine sleep-related cognitions and dysfunctional beliefs. Items such as “I am worried that I may lose control over my abilities to sleep” are scored on a 10-point Likert scale ranging from 0 to 10. Like the original 30-item version, the DBAS-16 has been found to reliably discriminate between self-reported good and poor sleepers in older adult populations with adequate internal consistency (Cronbach α=.79 for research samples). A DBAS score of 4 or above is indicative of a clinically significant level of dysfunctional beliefs around sleep [21].

The Pittsburgh Sleep Quality Index [43] consists of 19 items and examines sleep quality and disturbances over the past month. The first 4 questions are open, whereas items 5 to 19 are rated on a 4-point Likert scale. Individual item scores from the 7 sections are calculated first, and those 7 component scores are subsequently added up to calculate the global score ranging from 0 to 21. A sleep score of >5 is indicative of poor sleep quality. The Pittsburgh Sleep Quality Index measures sleep quality in a broader sense than just insomnia severity and has good internal consistency (Cronbach α=.83).

The Insomnia Severity Index [44,45] is a brief self-report questionnaire used to measure the severity of insomnia, impairment of daytime functioning, and worry about sleep over the past 2 weeks. It examines both nighttime and daytime components of insomnia and is increasingly used in research as an instrument to examine treatment response. The Insomnia Severity Index has been shown to have excellent internal consistency in community samples (Cronbach α=.90).

The Glasgow Sleep Effort Scale [36] reviews sleep effort. Sleep effort is a concept that explains a person’s voluntary effort to control a partially involuntary process, namely falling asleep. The Glasgow Sleep Effort Scale consists of 7 items, for example, “I put too much effort into sleeping when it should come naturally,” rated on a 3-point scale (“very much”, “to some extent”, and “not at all”). Internal consistency was reported as fair, with Cronbach α=.77 [36].

The Self-Efficacy for Sleep Scale [37] assesses the “belief people have in their ability to participate in certain behaviors needed to promote their health” [46,47]. The Self-Efficacy for Sleep Scale is a 9-item measure of how confident an individual is to carry out a variety of behaviors related to sleep, for example, “fall asleep at night in less than 30 minutes.” Items are scored on a 5-point scale, with higher scores being indicative of increased sleep self-efficacy. The SES has fair internal consistency (Cronbach α=.71) [48].

The Sleep Locus of Control Scale [38] is an 8-item measure that examines the internal sleep locus of control, the belief that sleep outcomes are dependent on one’s behavior on a 6-point Likert scale. The Sleep Locus of Control Scale contains 2 subscales, internal locus of control and chance sleep locus, and is reported to have internal consistency of Cronbach α=.72 (internal locus of control) and .59 (chance sleep locus) [38].

Hyperarousal will be assessed using the Pre-Sleep Arousal Scale (PSAS) [35]. The PSAS measures cognitive and somatic symptoms of arousal before falling asleep using 2 subscales. The 2 subscales each consist of 8 items. The items are rated using a 5-point Likert scale, with scores ranging from 1 to 5. The internal consistency of the PSAS has been reported as Cronbach α=.67 for the cognitive and .84 for the somatic subscales in normal sleepers and .76 and .81, respectively, for individuals with insomnia.

The Morningness-Eveningness Questionnaire [40] assesses chronotype. The 19-item scale was developed to examine individuals’ alertness at specific times of the day. The 19-item scale examines preferences in sleep and wake times and what times of the day subjects feel most alert. The Morningness-Eveningness Questionnaire has shown sufficient internal consistency for the original (Cronbach α=.82) as well as for the reduced version [49].

The Sleep-Related Behaviors Questionnaire [39] is a 32-item instrument that assesses safety behaviors relating to sleep; for example, “I miss or cancel appointments (daytime or evening).” Items are rated on a 5-point scale ranging from 0 (meaning “almost never”) to 4 (meaning almost always”). The questionnaire has high internal consistency (Cronbach α=.92).

Participants will wear an actigraph and complete a sleep diary over 96 hours (72 hours plus an additional 24 hours to account for nonadherence wear time). Actigraphic sleep assessment will assess sleep onset latency, wake-after-sleep onset, total sleep time, and the number of nighttime awakenings. The Actigraph model wGT3X-BT activity monitor (ActiGraph) will be used. Actigraphy has been recognized by the American Academy of Sleep Medicine as an appropriate method for assessing sleep. However, when compared with polysomnography, actigraphy has lower accuracy in detecting wake periods; especially in individuals with poor sleep quality [50]. The actigraphy data will be manually scored along with a sleep diary. This process was recommended by Boyne et al [51] to optimize agreement with polysomnography-measured sleep-wake. Additionally, the Choi algorithm will be used to differentiate between wear and nonwear times, which more accurately estimates time spent sedentary than other algorithms [52]. The sleep diary is a modified version of the Consensus Sleep Diary [53], which, in addition to the questions covered by the Consensus Sleep Diary, records the total duration of all daytime naps, how many times the study participant got up during the night, what time they had planned to wake up at, and whether they took any sleep medication.

Participants will be grouped into 4 sleep groups: noncomplaining good sleepers, complaining good sleepers, noncomplaining poor sleepers, and complaining poor sleepers. Participants will be grouped based on their actigraphy results and sleep complaint status (complaining versus noncomplaining sleepers), with participants appraised as poor sleepers if their sleep onset latency or wake-after-sleep onset is ≥31 minutes, 3 times or more during the recording period (as per actigraph recording). A participant will be considered a complaining sleeper if they report having had a sleep problem (eg, trouble falling asleep) for a minimum of 6 months at baseline data collection [5,54].

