## Introduction

Sleep problems, such as insomnia, are highly prevalent in those older than 60 years of age [1], with age-related changes in sleep architecture appearing from middle age and continuing to remain relatively constant past the age of 60 years [2]. Insomnia is characterized by difficulties with sleep initiation, duration, or quality that are not due to a lack of opportunity to sleep and which results in daytime impairment [3]. It is classified as chronic when it occurs at least 3 times per week and persists for more than 3 months [4]. Furthermore, a diagnosis of insomnia consists of 2 components: sleep quality and sleep appraisal. Sleep quality can be good or poor and sleep appraisal can be characterized by the presence or absence of a sleep complaint. These 2 factors have been described as being independent of each other [5], and in about 25%-35% of individuals, sleep quality and sleep appraisal are asynchronous and uncoupled [6]. It has been proposed that such uncoupling of sleep quality and sleep complaints may be prevalent among older adults [7,8]. In their seminal study examining poor sleepers that do not complain of insomnia, Fichten et al [9] first observed the asynchrony of sleep complaints and sleep patterns in older individuals. They reported that daytime impairment, assessed as sleepiness and daytime fatigue was higher in high-distress poor sleepers than in low-distress poor sleepers, and that low-distress poor sleepers experienced the same levels of daytime impairment as good sleepers.

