### Procedure

Participants who express an interest in participating will be contacted to make an appointment for a screening call. During the screening call, potential participants will be provided with information about the study and will be assessed against the eligibility criteria. Once a potential participant is confirmed to be eligible, they will complete, sign, and return the consent form. Upon study commencement, potential participants will be provided with an individual web-based link to the Qualtrics questionnaire battery (Qualtrics XM Platform software, Qualtrics). Once the questionnaire has been completed, actigraphs will be posted to participants using a courier service. Delivery and collection times will be arranged before dispatch at a time convenient for the participant. Where courier services are not available, the sleep watches will be posted by registered express mail, including a prepaid self-addressed return envelope. Study participants will be required to wear an actigraph on their nondominant wrist for 96 hours, except when they take a bath, have a shower, go swimming, or undergo any other activity that would result in them submerging the actigraph in water. They will also be instructed to record the exact time when they remove the actigraph and, subsequently, when they reattach the actigraph to their wrist in their sleep diary. This allows for accurate matching of the actigraph-estimated wear and nonwear times with the sleep diary. The sleep diary will be completed concurrently to record bedtimes, sleep and wake times, frequency and duration of nocturnal awakenings, rise times, daytime naps, and nonwear times, and will be returned with the actigraph after the measurement has been completed. A printed copy of the sleep diary will allow the participant to keep the diary on their bedside table so the relevant sections can be completed upon going to bed and waking up in the morning.

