### Statistical Analysis

An a priori power analysis using the program G*Power was performed to assess whether the study will have enough power to detect significant differences in sleep outcomes between the study groups [60]. We calculated that a sample size of 40 would be sufficient to detect this size effect. In order to account for attrition rates and missing data, a minimum of 60 participants will be recruited for the study.

Since sleep complaint status (sleep problem, eg, initial insomnia, for a minimum of 6 months) is used to classify participants as complaining or noncomplaining sleepers, multivariate ANOVA will be conducted separately to examine subjective and objective sleep quality for the 4 sleep groups. The multivariate ANOVA enables the analysis of multiple continuous dependent variables simultaneously (eg, sleep onset latency, wake-after-sleep onset, total sleep time, and the number of nighttime awakenings). In addition, a mediation analysis will be performed to determine whether sleep improvements following web-based CBT-I are the result of changes in sleep-related beliefs or other factors in older adults living in the community. Mediation analysis will be carried out using the bootstrapping method in the Hayes Process Macro for mediation, moderation, and conditional analysis for SPSS (version 28.0; IBM Corp) [61,62].

Actigraphy measures will be scored using the Cole-Kripke algorithm, which is suitable for use with older populations [63] and using ActiLife software (ActiLife 6 software, Version 6.13.1, ActiGraph). The autoscored data will be manually compared with the sleep diary to determine any incongruence between the actigraph measurements and the sleep diary.

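### The poor-sleeper rule sets a fixed count of 3 against a recording that yields 3 or 4 valid nights, so group membership depends partly on lost wear

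*Protocol article*

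**What the plan says.** The Design section sets the actigraphy recording at "96 hours (72 hours plus an additional 24 hours to account for nonadherence wear time", and the Procedure section repeats the requirement: "Study participants will be required to wear an actigraph on their nondominant wrist for 96 hours". Removal is allowed for bathing, swimming and similar activities and is logged in the diary. Non-wear is detected by software: "the Choi algorithm will be used to differentiate between wear and nonwear times".

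The objective half of the grouping has "participants appraised as poor sleepers if their sleep onset latency or wake-after-sleep onset is ≥31 minutes, 3 times or more during the recording period". It is crossed with complaint status (a sleep problem for at least 6 months) to give four groups. The article does not link the count of 3 to the number of valid nights.

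The Statistical Analysis section then uses the groups as the comparison factor: "multivariate ANOVA will be conducted separately to examine subjective and objective sleep quality for the 4 sleep groups". The Introduction also makes the prevalence of asynchronous sleepers a phase 1 result, and the Conclusions single out complaining good sleepers as a particular concern.

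**The concern.** The numerator of the rule is fixed and its denominator is not. The extra 24 hours exist because some participants are expected to lose wear time, so the plan itself foresees participants with different numbers of usable nights. The rule is stricter for those with fewer nights. Two people with the same sleep can then fall into different groups because one of them lost a night of recording.

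The label defines who counts as asynchronous. Removing a night can lower the count of bad nights but never raise it. A complainer who loses the label poor becomes a complaining good sleeper, and a noncomplainer who loses it becomes a noncomplaining good sleeper. The prevalence estimate and the contrasts between the four groups both take in this shift. With 65 participants spread over four groups, a few changes of label could matter.

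**Working it through.** **Inputs from the article**
- Recording: 72 + 24 = 96 hours; 96/24 = 4 nights at most; 72/24 = 3 nights if the reserve is used up.
- Rule: at least 3 occurrences of sleep onset latency (SOL) or wake-after-sleep onset (WASO) ≥31 minutes.

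**Assumed inputs (not in the article)**
- p, the probability that a night is bad (SOL or WASO ≥31 minutes), from 0.2 to 0.9.
- Nights are independent, and a bad night counts once.

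**Step 1: share of bad nights required**
- 4 valid nights: 3/4 = 75%.
- 3 valid nights: 3/3 = 100%.
- 2 valid nights: 3 bad nights cannot occur.

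**Step 2: chance of being labelled poor**
- 3 nights: p³.
- 4 nights: 4p³(1 − p) + p⁴.
- Ratio of the two: 4(1 − p) + p = 4 − 3p.

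| p | 4 valid nights | 3 valid nights | Ratio |
|---|---|---|---|
| 0.2 | 0.027 | 0.008 | 3.4 |
| 0.5 | 0.313 | 0.125 | 2.5 |
| 0.6 | 0.475 | 0.216 | 2.2 |
| 0.7 | 0.652 | 0.343 | 1.9 |
| 0.9 | 0.948 | 0.729 | 1.3 |

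For p = 0.6: 4 × 0.216 × 0.4 + 0.1296 = 0.4752, against 0.6³ = 0.216.

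**Step 3: a check that needs neither p nor independence between nights**

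Take someone with exactly 3 bad nights of 4, who is poor under full wear. If one night is lost at random, it is a bad one with probability 3/4. Two bad nights of 3 then remain and the label becomes good. Someone with 4 bad nights of 4 keeps the label. Someone with 2 or fewer was never poor. All movement is therefore from poor to good. At p = 0.5 this agrees with Step 2: 0.0625 + 0.25 × 1/4 = 0.125.

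**Step 4: the other reading of the count**

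The rule counts times, not nights. Suppose SOL and WASO exceedances on one night count separately, are independent and equally likely, and at least one occurs with probability 3/7. Each then has probability 1 − √(4/7) = 0.244. The chance of at least 3 exceedances is 0.31 with 4 nights (8 chances), 0.16 with 3 (6 chances) and 0.05 with 2 (4 chances). The 75% and 100% figures no longer apply, but the dependence on valid nights remains.

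**The case against.** The strongest reply is that the fourth day exists to absorb non-wear, that the permitted removals are for water activities and need not cost a night, and that a condensed article may leave the handling of valid nights to a fuller protocol. The article gives no bad-night probability and no count of lost nights, so the number of participants affected is unknown. This limits the size of the effect but does not remove it. A reserve that some participants use and others do not is what makes the denominator vary, and the rule as printed does not adjust for it.

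Four stronger readings are tempting, and the article does not support them.
- **The rule contradicts the article's own frequency criterion.** The Introduction says of insomnia: "It is classified as chronic when it occurs at least 3 times per week and persists for more than 3 months". Three in 7 is 43% of nights, well below 75% or 100%. But that sentence defines chronic insomnia and is nowhere offered as the standard for the actigraphic rule. It is context only.
- **All misclassification runs from poor to good.** Only the effect of a lost night does. With 4 nights, someone with p = 0.3 is still labelled poor 8% of the time, so chance errors run both ways.
- **Every analysis is affected.** The mediation analysis is not described as grouped. The prevalence and the group comparisons are affected.
- **Adherence differs between groups.** Nothing in the article says so, and the problem does not require it.

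It is also fair to object that a mean-based rule changes the construct. WASO of 95, 0 and 0 minutes averages 31.7, so a single night would make the participant poor. Such a rule therefore belongs in a sensitivity analysis and should not simply replace the printed one.

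**Conclusion.** The point holds as a should-fix. As printed, the rule makes the good/poor label depend on how many nights were validly recorded. Under per-night counting and independent nights, losing one night divides the chance of being labelled poor by 4 − 3p: about 1.9 to 2.5 for p between 0.7 and 0.5, and 1.3 to 3.4 over p from 0.9 to 0.2. With 2 valid nights the label is unattainable. The direction of the lost-night effect is certain. Its size in this trial depends on how many participants lost a night, which the article does not report.

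**What to change.** 1. State that SOL and WASO exceedances on the same night count once.
2. Tie the threshold to valid nights, through either a common number of nights for everyone or a fixed proportion of them. Two cautions apply. Keeping the count at 3 while using exactly 3 nights would demand 100% bad nights of everyone. With so few nights a proportion removes the dependence only in part: 75% of 3 nights is 2.25, which rounds up to 3 of 3 again. Only a common number of nights equalises the requirement fully.
3. Do not label as good a participant with too few valid nights to meet the count. Report such participants as unclassifiable.
4. Report valid nights by group, and the number of participants with 3 valid nights of which exactly 2 were bad. Under the printed rule, these are the only participants with 3 valid nights whose label the missing night could have changed.
5. As a sensitivity analysis, repeat the prevalence estimate and group comparisons under a rule independent of the number of valid nights (for example, mean SOL or mean WASO ≥31 minutes), and report how many participants change group.

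The cost is small, since the nightly data already exist. A few participants may change group or become unclassifiable. Because the analyses of both phases are reported as finished, any alternative rule must be labelled post hoc.

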### Procedure

Participants who express an interest in participating will be contacted to make an appointment for a screening call. During the screening call, potential participants will be provided with information about the study and will be assessed against the eligibility criteria. Once a potential participant is confirmed to be eligible, they will complete, sign, and return the consent form. Upon study commencement, potential participants will be provided with an individual web-based link to the Qualtrics questionnaire battery (Qualtrics XM Platform software, Qualtrics). Once the questionnaire has been completed, actigraphs will be posted to participants using a courier service. Delivery and collection times will be arranged before dispatch at a time convenient for the participant. Where courier services are not available, the sleep watches will be posted by registered express mail, including a prepaid self-addressed return envelope. Study participants will be required to wear an actigraph on their nondominant wrist for 96 hours, except when they take a bath, have a shower, go swimming, or undergo any other activity that would result in them submerging the actigraph in water. They will also be instructed to record the exact time when they remove the actigraph and, subsequently, when they reattach the actigraph to their wrist in their sleep diary. This allows for accurate matching of the actigraph-estimated wear and nonwear times with the sleep diary. The sleep diary will be completed concurrently to record bedtimes, sleep and wake times, frequency and duration of nocturnal awakenings, rise times, daytime naps, and nonwear times, and will be returned with the actigraph after the measurement has been completed. A printed copy of the sleep diary will allow the participant to keep the diary on their bedside table so the relevant sections can be completed upon going to bed and waking up in the morning.

Following the baseline assessment, including the recording of demographic information and sleep complaints, the administration of the questionnaires, and actigraphy measurement, all groups will receive identical instructions for the web-based CBT-I program. Participants will be required to complete the 4 sessions plus homework of the program within 4 weeks. Participants will receive weekly email reminders from the principal investigator to confirm the completion of each of the 4 CBT-I modules. Once the completion of the CBT-I program has been confirmed with the participant, actigraphy, sleep diary, and questionnaire measurements will be repeated posttreatment. The study process is shown in Figure 1.

